## Safety Oversight (ISM plus SMC)

The Safety Oversight in this study will be under the direction of both Independent Safety Monitor (ISM) and the Safety Monitoring Committee (SMC).

Independent Safety Monitor

The ISM is a physician with relevant expertise, whose primary responsibility is to provide independent safety monitoring in a timely fashion. Participation is for the duration of the study and the ISM is appointed by the sponsor. The ISM should be able to access participant records readily in real time. The primary focus of the ISM is to independently review serious adverse events that may be associated with product and adverse events of special interest. The ISM should investigate those events considered serious and unexpected. Clinical and laboratory data, clinical records and other study-related records should be made available for ISM review. It is the responsibility of the CI to ensure that that the ISM is appraised of all new safety information relevant to the study product and the study. This includes providing the ISM with a copy of the Clinical Investigator’s Brochure (CIB) in advance, as well as promptly providing all CIB revisions and all other safety information issued by the sponsor that is received by the CI. The ISM should receive all protocol revisions and may receive other documents related to the study.

The ISM will be in communication with the CI at the enrollment site and the SMC chair for any event that needs further evaluation.

The ISM together with the clinical investigator (CI) will be also involved in the review of all reactions including the solicited events that have occurred within the observation window for the two participants that will initially receive the study product. The ISM will also be involved in the decision making by SMC on whether the remaining participants will receive the first dose.

The ISM will not be directly involved with the trial and is not under the CI’s supervision and has no financial, intellectual, proprietary or professional interest in outcome of the trial.

Safety Monitoring Committee

The SMC will be composed of the ISM, an infectious diseases physician, a physician with expertise in clinical trials or vaccine studies and a cardiologist. The safety of each dose of the vaccine candidate through Day 28 in the 20 participants will be evaluated by the SMC following a review of a clinical and laboratory safety data package. The SMC will also review the recorded AEs and SAEs. The SMC makes recommendations to the sponsor. These recommendations are approved by the SMC chair who signs a letter of recommendation that is sent to the CI.

In regards to the safety review of the first dose, the SMC will provide recommendations to the sponsor for administration of the second dose. These recommendations will be communicated to the CI, PI and QIMR-HREC prior to administration of the second dose. There will also be a safety review by the SMC after the second dose with recommendations regarding the continuation or modification of the study.

Additionally, the SMC will meet to assess any events that trigger the halting rules or as needed to provide a recommendation and findings to QIMR-HREC, the PI and the CI, in accordance to the approved SMC charter.

Whether at a scheduled or unscheduled meeting, the SMC will consider safety signals to determine whether or not they can recommend that the study continue.

# Clinical Monitoring

The sponsor is responsible to ensure that this clinical study is monitored adequately and that it is being conducted in accordance to this protocol and regulatory requirements.

The monitoring visits will be in accordance to the current QIMR standard operating procedures and the outsourced CROs.

## Site Monitoring Plan

Site monitoring is conducted to ensure the human subject protection, study procedures, laboratory, study intervention administration, and data collection processes are of high quality and meet sponsor, GCP/ICH and, when appropriate, regulatory guidelines. Site visits may be conducted by an authorized representative of QIMR or other regulatory agencies to inspect study data, participants’ medical records, and CRFs in accordance with ICH guidelines, GCP and the respective local and national government regulations and guidelines.

The investigator will permit authorized representatives of QIMR and the respective local and national health authorities to inspect facilities and records relevant to this study if needed.

The monitoring visits will be conducted as specified in the site monitoring plan. Briefly, the monitoring visits will be conducted before, during and after the trial. However, the sponsor for TGA QIMR have authority to request initiation of additional monitoring visits.

In QIMR-sponsored trials, all activities associated with site initiation and monitoring will be outsourced to a Contract Research Organization (CRO). The monitor will visit the CI at the site of investigation to ensure that all requirements are being met as specified in this protocol. The CI will ensure that all follow up actions are sufficiently addressed and/or completed and appropriately documented within the recommended timeframe.

# Statistical Considerations

## Introduction

Group A Streptococcus (GAS) is a serious human pathogen that affects people of all ages and socioeconomic backgrounds. Common GAS infections include streptococcal pharyngitis and pyoderma, which are particularly common in children. Far more serious infections of GAS include necrotizing fasciitis, pneumonia, and toxic shock syndrome, primarily affecting the elderly. Post-streptococcal sequelae include rheumatic fever, rheumatic heart disease, and acute glomerulonephritis.

## Overview and Study Objectives

This study is a randomized, double-blinded, controlled Phase I clinical trial to evaluate the safety and immunogenicity of a Group A Streptococcus Vaccine in a novel J8-D/alum formulation performed in healthy adult participants from Brisbane, Australia. Twenty participants will be randomized in a 3:1 ratio to receive either two injections each containing 50 μg of the vaccine candidate or two injections of saline at eight-week intervals.

### Primary Outcome Measures

The primary objectives of this study are to:

• Evaluate the safety of a Group A Streptococcus vaccine candidate delivered intramuscularly to healthy adults in two doses of 50 μg AcJ8-D adsorbed onto alum.

Safety of the vaccine candidate will be assessed on the basis of the frequency and occurrence of injection site and systemic reactions following administration of the investigational vaccine. Safety parameters include changes in clinical biochemistry and hematology values on blood and urine, and changes in electrocardiogram and transthoracic echocardiograms. Adverse events and serious adverse events will be reported throughout the duration of the study.

### Secondary Outcome Measures

The secondary objective of this study is to assess the immunogenicity of a group A streptococcus vaccine candidate delivered intramuscularly in two doses of 50 µg AcJ8-D adsorbed onto alum.

The immune response to the AcJ8-D vaccine will be assessed by:

• Monitoring for the presence of vaccine-specific antibodies in all participants of the study and the titer of the vaccine-specific antibodies after each administered dose of the vaccine candidate, to investigate the relationship between the doses administered and the titer of vaccine-specific antibodies.

• Measuring the bactericidal activity of the induced antibodies against different standard reference strains of Group A Streptococcus such as M1, M6, and 88/30.

## Study Population

This study will be conducted in twenty healthy adults, both male and female, between the ages of 18-45 years, inclusive. Participants will be from the Brisbane, Australia area. Additionally, participants must have normal electrocardiogram and echocardiogram results and have no personal or family history of post-streptococcal or collagen-vascular disease.

## Study Design

This study is a double blind, randomized Phase I single cohort clinical trial with N=20 participants. The participants will be randomized 3:1 to receive either the investigational vaccine (N=15) or the control (saline, N=5. Each participant will receive a total of two injections at eight-week intervals.

Screening is expected to take three weeks, starting at Day -28. At Day 0, two sentinel participants will be enrolled and randomly selected to receive either the investigational vaccine or the control saline 24 hours before all other participants. Assuming that no immediate serious adverse reactions are observed in these sentinel participants, the remaining 18 participants will be enrolled and dosed. The sentinel participants will receive their second dose at the same time as the remaining participants.

Each participant will receive two injections administered at eight-week intervals with a safety review following each injection. The SMC review will include data on:

- Reactogenicity at one-week post-study product administration;
- Hematology, chemistry, and urinalysis at four weeks post-study product administration, and
- ECG and ECHO at four weeks post-study product administration.

Data will be collected for review at five weeks post-initial dose with an SMC review in the seventh week. There will be at least seven days between the SMC review and the next injection to permit adequate review of post-product administration safety data.

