| **Description of Study Design:** | The purpose of this study is to evaluate the safety and immunogenicity of a Group A Streptococcus vaccine candidate. The participants (N=20) will be randomized 3:1 to receive the active intervention (N=15) or saline as placebo control (N=5). Participants randomized for intervention will receive either 50 µg of the vaccine candidate or saline. 2 participants will be dosed, 1 placebo and 1 investigational product 24 hours before the remaining 18 participants. They will be observed for 6 hours for any immediate adverse events. The ISM will review the data prior to the other 18 participants receiving study product. If no immediate serious adverse reactions have been observed the other 18 participants will receive an intramuscular injection of 0.5mL volume of the assigned study product. Safety of the first dose will be assessed by the Safety Monitoring Committee (SMC) before proceeding to administering the second dose to all 20 participants on Day 56. Clinical and adverse events/serious adverse event assessment will be conducted throughout the study at the scheduled clinic visits. Clinical specimens (urine and blood) will be collected from each participant to assess the safety and the immunogenicity of the investigational vaccine. Echocardiograms and electrocardiograms will be performed throughout the study to assess the safety of the vaccine formulation. |
| **Estimated Time to Complete Enrollment:** | The enrollment of all participants in this study will take approximately 4 weeks. |

**Schematic of Study Design**: Screening, Study Product Administration, Safety Testing, Safety Monitoring Committee Review for the cohort of 20 subjects

| **Vaccine Trial Schedule** | |
| --- | --- |
| **Time** (day) |  |
| Day -28 to Day -7 | Screening  ECG/ECHO/hematology/chemistry/urinalysis/ASOT/-DNAse B |
| Day 0^ | Dose 1 (n = 15A*, 5C*) |
| Day 8±2 | Memory aid completion |
|  |  |
| Day 28±7 | ECG/ECHO/hematology/chemistry/urinalysis/ASOT/-DNAse B |
| Day 35±5 | Database Collection of Data (up to Day 28 data) |
|  |  |
| Day 49±5 | SMC Dose 1 review |
| Day 56±5 | Dose 2 (n = 15A*, 5C*) |
| Day 64±2 | Memory aid completion |
|  |  |
| Day 84±7 | ECG/ECHO/hematology/chemistry/urinalysis/ASOT/-DNaseB |
| Day 98±5 | Database Collection of Data (up to Day 84 data) |
|  |  |
| Day 126±7 | SMC Dose 2 review |
|  |  |
| Day 180±14 | Follow up visit  Hematology/chemistry/urinalysis/ASOT/-DNAse B |
|  |  |

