# Study Design

This study is a double blinded, randomized Phase I single cohort clinical study (N = 20 participants). The participants will be randomized 3:1 to receive the intervention (N=15) or control (saline), (N=5). Each participant will receive a total of two injections with an 8-week interval between injections.

To investigate for the occurrence of any immediate serious adverse reactions to the injected vaccine candidate, two (2) participants (one randomized to receive the study vaccine and one to receive the control saline) will have study product administered 24 hours before the remaining eighteen (18) participants. These two participants will be observed for at least 6 hours after study product administration to evaluate that no immediate serious adverse reactions have occurred, by measuring vital signs, change in the baseline symptoms and monitoring for occurrence of clinically significant symptoms and adverse events, The clinical investigator (CI) and the Independent Safety Monitor (ISM) will review all reactions including the solicited events that have occurred within the observation window for these two participants following study product administration and decide on whether the remaining participants will receive the first dose. If no immediate serious adverse reactions have been observed, the remaining participants will receive the first dose. The clinical and the adverse events recorded at the scheduled interim visits will be assessed by the SMC to assess the safety of the vaccine candidate prior to proceeding to the second dose.

Throat swabs will be taken from each participant at screening and on each day of study product administration. Rapid antigen test (QuickVue In-Line Strep A test) for group A streptococci will also be performed for each participant prior to each study product administration. Targeted physical examinations including cardiac auscultation by a physician will be performed on the day of each study product administration. Each participant will be observed for 30 minutes following administration of study product for evidence of immediate reactions.

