**Day 0, (Day of Dose 1)**

Two participants, one randomized to receive vaccine study product and the other control saline will have study product administered 24 hours prior to the remaining 18 participants which may be split into 2 cohorts. The safety of the first dose in these two participants will be initially observed for at least 6 hours and evaluated by the clinical investigator and the ISM to make recommendation on whether to proceed with administration of the study product to the remaining 18 participants.

These 2 participants will follow the events listed in Day 0 and will be dosed on Day 56 as all the participants of the study.

The safety of the first dose of the vaccine candidate in the study participants will be evaluated by a SMC that will make a recommendation to proceed to the administration of the next vaccine dose. See section 4 for the vaccine candidate dosage schedule. Refer to Appendix A for a tabular presentation of the study procedures.

Procedures to be followed at enrollment:

1. Review study eligibility and record concomitant medications.

2. Review medical history for any change in status from screening

3. Record baseline symptoms and vital signs. If the participant is febrile (temperature >38°C [>100.4F] or has an acute illness, the dose must be rescheduled. If rescheduled, the study product administration must be within 28 days after all screening procedures.

4. Targeted physical examination including cardiac auscultation. Particular attention to any elicited symptoms and signs consistent with rheumatic fever i.e. rash, arthalgia/arthritis (joint pain/swelling), renal angle tenderness and cardiovascular examination and movement disorder.

5. Obtain a throat swab and conduct a rapid antigen test for group A streptococci

6. Collect urine for urinalysis and blood for hematology, biochemistry and serology including, ASOT, α-DNase B, detection of α-J8 peptide vaccine specific antibodies, blood sample for quantitative cellular response as well as serum samples for α-DT antibodies and safety serum storage (refer to appendix D for tests required and blood volumes).

7. For female participants ensure that adequate contraceptive precautions have been taken since the screening pregnancy test and ensure that a urine test for -HCG is negative.

8. Perform breath alcohol test and urine drug screen.

9. Administer the study product.

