## Halting Rules

Study product administration in the trial will be halted for expedited ISM/SMC review if, during the 7 days after product administration, any of the following occur:

• One (1) or more participants experiences an SAE that is unexpected and associated with study product administration

• 10% or more of the participants enrolled to date experience a severe (grade 3) study product associated fever

• 10% or more of the participants enrolled to date experience a severe (grade 3) study product associated local redness or induration;

• 10% or more of the participants enrolled to date experience a severe (grade 3) study product associated subjective reaction (pain, headache, malaise or myalgia), the severity of which is corroborated by study personnel

• One (1) or more participants experience a study product -associated bronchospasm or other anaphylactic response

• One (1) or more participants experience a study product-associated allergic event or vaccine site ulceration, abscesses or necrosis

The trial will be halted at any time if there is:

• Any patterns of laboratory values or clinical symptoms that the CI considers to be a significant safety issue for participants or any clinical symptoms of rheumatic carditis and/or rheumatic fever as defined by Jones criteria. (see Appendix G).

• ECG or ECHO abnormality such as:

- Increase in valvular regurgitation to greater than mild severity;
- Development of mitral regurgitation with an EROA of 20mm2 or >10mm2 increase from the baseline study;
- An absolute increase in effective regurgitant area of 10mm2 compared to baseline;
- Development of mitral regurgitation with an EROA > 20 mm2 and

echocardiographic criteria of probable RHD will require notification of the appropriate regulatory bodies as associated SAE.

- Any abnormal valve leaflet thickening (subjective);
- Worsening left ventricular systolic function (ejection fraction of < 50%);
- Left ventricular dilatation (based on LV diameter > upper limit of reference ranges for LV end diastolic diameter (LVEDd) indexed for body surface area (Females 24-32 mm/sqm; Males 22-31mm/sqm);
- Significant right ventricular dysfunction;
- Evidence of pulmonary hypertension (estimated RVSP > 40mmHg);
- Development of more than trivial pericardial effusion;

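### The gate between the two sentinels and the remaining 18 participants names conflicting deciders, and its go criterion is not reconciled with the halting rules

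*Protocol*

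**What the plan says.** **Who is dosed first.** The Protocol Summary states that "2 participants will be dosed, 1 placebo and 1 investigational product 24 hours before the remaining 18 participants". The schematic footnote and section 7.2 (Day 0) agree, and section 4 describes the pair as "one randomized to receive the study vaccine and one to receive the control saline". Section 11.4 is looser: "two sentinel participants will be enrolled and randomly selected to receive either the investigational vaccine or the control saline 24 hours before all other participants".

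**When the others may be dosed.** Section 4 has the CI and the ISM review every reaction in the sentinels' observation window, solicited events included, and decide. It then adds: "If no immediate serious adverse reactions have been observed, the remaining participants will receive the first dose". The Summary and section 11.4 use the same criterion of no immediate serious reaction.

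**When dosing is halted.** Section 9.5 halts administration for expedited ISM/SMC review if certain events occur within 7 days of dosing. One trigger is "10% or more of the participants enrolled to date experience a severe (grade 3) study product associated fever". Parallel 10% triggers cover related grade 3 redness or induration and related grade 3 subjective reactions. Other triggers need only one participant, among them a related allergic event.

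**Who decides.** Section 4 gives the decision to the CI and ISM. Section 7.2 has the same two make a recommendation, without naming its recipient. The Summary mentions only an ISM review. Section 9.6 says: "The ISM will also be involved in the decision making by SMC on whether the remaining participants will receive the first dose".

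**The concern.** The sentinel step is the only planned stagger between the first exposure and the dosing of the other 18. Staff should know beforehand who gives the release and on what basis. The protocol leaves both open.

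The time is short. The sentinels are observed for at least 6 hours and the others follow 24 hours after them, which leaves about 24 − 6 = 18 hours. Whether a committee must be convened in that interval cannot be left to interpretation on the day.

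The criterion matters in the same way. If a sentinel has a related reaction that is severe but not serious, one team could follow section 4 and dose the other 18, and another could follow section 9.5 and stop. Both would be following the protocol.

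**Working it through.** **1. The plan's own allocation.** Section 11.4: 20 participants at 3:1 gives 20 × 3/4 = 15 vaccine and 20 × 1/4 = 5 saline, as stated. One sentinel per arm leaves 15 − 1 = 14 vaccine and 5 − 1 = 4 saline, and 14 + 4 = 18, the stated remainder.

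**2. The deciding body, side by side.**

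| Place in the protocol | Who acts | Role |
| --- | --- | --- |
| Summary, description of study design | ISM | reviews the data |
| Section 4 | CI and ISM | decide |
| Section 7.2, Day 0 | CI and ISM | make a recommendation |
| Section 9.6 | SMC, with the ISM involved | decision making |

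These are not the same people under different names. Section 9.6 lists the SMC as the ISM, an infectious diseases physician, a physician with trial or vaccine expertise, and a cardiologist. The CI is not on that list. Section 4 therefore gives half of the decision to someone outside the body that section 9.6 refers to.

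**3. The criterion, tested on two outcomes.**

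- *A related fever of 39.0 to 40 °C in one sentinel.* The grading table in section 9.2.1 makes this grade 3. It does not by itself meet the serious adverse event definition in section 9.2.2. Sections 4 and 11.4 and the Summary say proceed. Section 9.5 depends on the denominator (step 4).
- *A related allergic event in one sentinel that is not serious.* The same three places say proceed. Section 9.5 says halt for review, because one participant is enough and seriousness is not required.

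**4. The 10% rule at the sentinel step.** The rule is met when events ÷ number enrolled so far ≥ 0.10.

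| Number enrolled | One event as a share | Smallest number of events that meets 10% |
| --- | --- | --- |
| 2 | 1/2 = 50% | 1 |
| 10 | 1/10 = 10% | 1 |
| 11 | 1/11 = 9.1% | 2 |
| 20 | 1/20 = 5% | 2 |

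The documents do not settle which row applies:

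- Section 11.4 has the remaining 18 enrolled and dosed after the sentinels have been cleared, which points to 2.
- Section 5 obtains consent to the interventional part once suitability is confirmed at screening, and the Summary allows about 4 weeks for enrolment. That could put up to 20 on the count before the sentinels are dosed.

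On the first reading one grade 3 event halts; on the second it does not.

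**The case against.** The strongest reply is that the rules can operate together. The CI and ISM already review all sentinel reactions, not only serious ones. Section 9.5 is a pause for expedited review, not a termination, and nothing switches it off at this step. The ISM sits on the SMC and has real-time access to records. A recommendation under section 7.2 could feed an SMC decision under section 9.6, so that only section 4 is out of line.

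Much of this stands, and it lowers the practical risk: a careful team would probably stop and ask. It does not remove the inconsistency. Section 4 follows its review of all reactions with an unconditional statement that the others will be dosed absent a serious one. No section says that the halting rules take precedence or refers the sentinel step to them. A team that treats section 4 as sufficient is not disobeying the text.

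A reader might also infer more from section 11.4: that each sentinel is randomised independently of the other, so that the intended pair often fails to occur. From an unrestricted 15:5 list, one of each would come up with probability 2 × 15 × 5 ÷ (20 × 19) = 39.5%. The documents do not support this as a finding. Four places fix one vaccine and one saline sentinel, and section 11.4 can be read as chance deciding which of the two gets which product. Section 5.3.1 does not say that the list is unrestricted, and list detail may properly sit in another document.

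Nor can confounding of arm with dosing day be inferred from section 7.2's mention of "the remaining 18 participants which may be split into 2 cohorts". No cohort sizes or dosing interval are given, and the analysis is descriptive.

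**Conclusion.** The point holds as an inconsistency in the sentinel gate, in two firm parts.

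- **Decider.** Section 4 (CI and ISM decide) conflicts with section 9.6 (SMC decision making). Section 7.2 and the Summary give further variants.
- **Criterion.** A related grade 3 reaction in one sentinel that is not serious is a proceed under section 4 and, with two enrolled, a halt under section 9.5 (50% against 10%). With 20 enrolled the share is 5% and that trigger is not met. The conflict does not depend on the denominator for a non-serious related allergic event, where one case halts.

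The grade 3 part rests on the two-enrolled reading of section 11.4, which the text supports but does not define. The allocation sentence in section 11.4 is loose wording to be aligned, not a contradiction, and no failure probability attaches to it.

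The effect is on conduct and participant safety before 18 people are dosed, not on the descriptive analysis. It should be corrected before the first dose.

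**What to change.** 1. Name one body that gives the release, and state whether others advise it. Make the Summary and sections 4, 7.2 and 9.6 agree.
2. In the Summary and sections 4 and 11.4, state how the criterion of no immediate serious reaction relates to section 9.5, with a cross-reference. Which clinical threshold governs is for the sponsor and its safety bodies.
3. In section 9.5, define who counts as enrolled when the 10% rules are applied at the sentinel step.
4. In section 11.4, say that one sentinel receives vaccine and one saline, leaving 14 and 4 among the other 18.

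The cost is a wording amendment and its ethics review. Sample size, allocation ratio and analysis are unchanged. Item 3 obliges the sponsor to choose a denominator, and that choice determines whether one grade 3 event at this step triggers a pause.
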